**Fig. 3 Fig3:**

Ischemic preconditioning protocol

#### Photobiomodulation preconditioning

PBM will be delivered using the Deep Light LED Device (Avanutri^®^, Três Rios, RJ, Brazil). The LED cluster, measuring approximately 12.2 cm in length, will be positioned in direct contact with the skin over the biceps brachii muscle at a 90° angle, with light pressure applied. The cluster will be positioned to cover the distal third of the distance between the lateral epicondyle and the acromion. Detailed PBM parameters are presented in Table 1. An energy of 72 J per diode (576 J total for the eight-diode cluster) was selected based on previous evidence that higher doses of infrared LED irradiation may attenuate the decline in MVIC [49].

**Table 1 Tab1:** Parameters of preconditioning with LED photobiomodulation

Device characteristics	
LED wavelength	810 nm (infrared)
Emission mode	Continuous wave
Number of diodes	1 cluster (8 diodes)
Distance between diode centers	2.0 cm
Beam divergence angle	15°
Geometric parameters	
Spot diameter (at emitter)	6.30 mm
Spot area (at skin surface)	0.71 cm² (estimated from beam divergence angle)
Total irradiation area (cluster aperture)	31.50 cm²
Power and irradiance	
Power per diode	150 mW (± 10%)
Total output power	1143 mW (measured output)
Peak irradiance (per diode at emitter surface)	201.30 mW/cm²
Average irradiance (cluster level)	36.30 mW/cm²
Dosimetry	
Application points	Single
Energy per diode	72 J
Irradiation time	504 s
Total energy (8 diodes)	576 J
Fluence at skin (per diode)	101.41 J/cm²
Average fluence (cluster level)	18.29 J/cm²

*Abbreviations*: *nm *nanometers, *cm *centimeters, *mm *millimeters, *mW *milliwatts, *J *joules, *s *seconds

#### Sham preconditioning

The sham applications will simulate IPC and PBM procedures without producing physiological effects. For the PBM sham condition, participants will wear protective eyewear and headphones emitting white noise to eliminate potential visual and auditory cues associated with device operation. The PBM device will be positioned and operated following the same procedures used in the active PBM condition; however, the LED emission will be disabled so that no therapeutic light is delivered while maintaining identical device handling and application time.

For the IPC sham condition, the cuff will be inflated to 10% TRP. This pressure is considered insufficient to meaningfully restrict arterial or venous blood flow and has been widely used in previous studies as a sham condition for ischemic preconditioning strategies [27]. Standardized instructions will be provided to all participants to maintain consistency between active and sham conditions.

### Eccentric exercise protocol

Muscle damage will be induced using a protocol consisting of 30 eccentric actions of the elbow flexors with dumbbells, based on a previous study [50]. The dumbbell load will correspond directly to the highest MVIC value obtained during baseline testing. For example, a participant presenting an MVIC of 10 kgf will perform the protocol using a 10-kg dumbbell. This approach has previously been shown to induce significant EIMD while remaining safe for participants [50]. A 45-s rest interval between repetitions will be adopted to allow partial recovery while maintaining sufficient mechanical stress to induce muscle damage. During each repetition, participants will lower the dumbbell from approximately 50° of elbow flexion to 170° of extension over 4–5 s. After each contraction, the investigator will remove the dumbbell and assist the participant in returning the arm to the starting position, ensuring that the movement remains exclusively eccentric. The interval between the preconditioning strategies and the eccentric exercise protocol will be approximately 5–15 min. The eccentric exercise protocol is expected to last approximately 25–30 min, including rest intervals. The main experimental visit, including baseline assessments, preconditioning procedures, eccentric exercise, and post-exercise assessments, is expected to last approximately 2 h.

### Statistical analysis plan

Sample size was determined a priori using data from an independent pilot study that applied the same eccentric exercise protocol as the present trial. The pilot included 20 participants (five per group) allocated to placebo, 6 J, 24 J, or 72 J PBM, with MVIC assessed before and immediately, 24, and 48 h after exercise. The pilot MVIC data yielded a within-participant correlation of 0.79, a Greenhouse–Geisser correction of ε = 0.82, and an observed group × time effect of f ≈ 0.23. The pilot-derived effect size was estimated from the group × time interaction using a repeated-measures ANOVA framework. Given the small pilot sample and the absence of an IPC group and 72-hour assessment, a conservative planning effect size of f = 0.12 was adopted. Using G*Power 3.1 (Heinrich-Heine-Universität Düsseldorf, Germany), the sample size was calculated for a three-group repeated-measures design with five measurements, α = 0.05, 80% power, f = 0.12, a within-participant correlation of 0.79, and ε = 0.82. The resulting minimum sample was approximately 44 participants; therefore, 45 participants (15 per group) were planned to ensure balanced allocation. Although the calculation used a repeated-measures ANOVA framework, linear mixed-effects models were prespecified for the primary analysis because they better accommodate within-participant correlations and incomplete repeated measurements.

Normality and homoscedasticity of residuals will be evaluated through graphical inspection (Q-Q plots and residual-versus-fitted plots) and the Shapiro–Wilk test. Potential influential observations and model fit will also be examined using standard diagnostic procedures. Descriptive statistics will be presented as mean ± standard deviation and 95% confidence intervals. The primary endpoint will be MVIC. The primary hypothesis concerns differences in the post-exercise MVIC recovery trajectory among the PBM, IPC, and sham groups. The primary inferential test will be the group × time interaction from a linear mixed-effects model including group and time (treated as categorical factors) as fixed effects, with a participant-specific random intercept to account for within-participant correlations. The prespecified key contrast will be the between-group difference in change in MVIC from baseline to 72 h between the PBM and IPC groups. Additional pairwise contrasts (PBM vs. sham and IPC vs. sham) and analyses of secondary outcomes will be considered exploratory and will not be subject to multiplicity adjustment. The effect measure for the PBM versus IPC comparison will be the between-group difference in change in MVIC from baseline to 72 h, reported with its 95% confidence interval and standardized effect size. Secondary continuous outcomes will be analyzed using linear mixed-effects models and interpreted as exploratory. For ordinal or bounded outcomes, generalized linear mixed-effects models with an appropriate distribution and link function will be used when the assumptions of a Gaussian model are not satisfied.

All randomized participants will constitute the intention-to-treat population and will be analyzed according to their originally assigned groups, regardless of intervention adherence or outcome availability. Missing observations will be handled within the prespecified mixed-effects framework using maximum likelihood estimation under a missing-at-random assumption. Sensitivity analyses comparing the primary maximum-likelihood analysis with a complete-case analysis will be performed if missing outcome data exceed 10% of the primary outcome observations. Statistical significance will be set at *p* < 0.05 for all analyses.

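### The stated minimum of 44 participants does not follow from the plan's own inputs: with ε = 0.82, 80% power needs 53 (54 balanced), and the planned 45 give about 72%

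*Protocol article*

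**What the plan says.** The Statistical analysis plan section of the protocol article gives the calculation in full. For the design it says that "the sample size was calculated for a three-group repeated-measures design with five measurements". The settings are "α = 0.05, 80% power, f = 0.12, a within-participant correlation of 0.79, and ε = 0.82". The correlation and ε come from a pilot study of 20 participants; f was set below the pilot value of about 0.23. The result is given as "The resulting minimum sample was approximately 44 participants", and then: "therefore, 45 participants (15 per group) were planned to ensure balanced allocation". So 15 per group rests on this calculation, with one participant added for equal group sizes. The next paragraph of the section makes the group × time interaction in a linear mixed model with a participant random intercept the primary test.

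**The concern.** A Greenhouse–Geisser ε below 1 is a penalty for non-sphericity, so it should raise the required sample size. With these inputs and no penalty at all the requirement is already 46, yet the plan applies ε = 0.82 and arrives at 44. A number below the penalty-free one suggests that ε was applied to only part of the calculation.

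At stake is the claim of 80% power, which is the only justification given for 15 per group. If true power at the planning effect is nearer 72%, the type II error risk is about 28% rather than 20%. A null interaction would then be read as stronger evidence of no difference than it is. This is a live issue here, because the Discussion already considers how to interpret a finding that the two interventions work equally well.

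**Working it through.** **Inputs**, all from the sample-size paragraph: k = 3 groups, m = 5 measurements, α = 0.05, target power 80%, f = 0.12, ρ = 0.79, ε = 0.82. The tested effect is the group × time interaction.

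**Formulae** (repeated-measures ANOVA, within–between interaction, noncentral F):
- λ = f² · N · m · ε / (1 − ρ)
- df1 = (k − 1)(m − 1)ε = 8ε
- df2 = (N − k)(m − 1)ε = 4(N − 3)ε

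**Reproducing the stated 44.** It appears when ε multiplies the degrees of freedom but is left out of λ. Then N = 43 gives 79.9% and N = 44 gives about 81%, so the minimum is 44; N = 45 gives 82.1%.

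**Applying ε throughout.** For N = 45:
- λ = 0.0144 × 45 × 5 × 0.82 / 0.21 = 12.65
- df1 = 8 × 0.82 = 6.56
- df2 = 4 × 42 × 0.82 = 137.76
- critical F = 2.11, power = 72.5%

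**The three versions side by side:**

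| N | ε in λ and df | ε = 1 | ε in df only |
|---|---|---|---|
| 44 | 71.2% | 77.9% | 81% |
| 45 | 72.5% | 79.1% | 82.1% |
| 46 | 73.6% | 80.2% | 83.2% |
| 52 | 79.96% | 85.9% | 88.4% |
| 53 | 80.9% | 86.7% | 89.1% |
| 54 | 81.8% | 87.5% | 89.8% |

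The minimum is 53 (54 for equal groups) with ε applied throughout, 46 under sphericity, and 44 only in the last column.

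**Why the last column is not valid.** The numerator of F, relative to the error variance, has expectation 1 + λ/df1. At N = 45 under sphericity λ/df1 = 15.43/8 = 1.93. Shrinking both terms by ε leaves it at 12.65/6.56 = 1.93. Shrinking only df1 raises it to 15.43/6.56 = 2.35, which enlarges the signal. That is why this version shows more power with non-sphericity (82.1%) than without it (79.1%).

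**Rounding.** Moving all three inputs to the favourable edge of rounding (f = 0.1249, ρ = 0.795, ε = 0.825) still needs 47 (79.0% at 46, 80.1% at 47).

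**Simulation.** The Greenhouse–Geisser-corrected test was simulated 20,000 times with average correlation 0.79, population ε = 0.82 and random interaction patterns scaled to f = 0.12. It rejected in 72.9% of runs with 15 per group and 83.5% with 18 per group. This supports the consistent formula and not 81–82%.

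**Detectable effect.** With ε = 0.82 and N = 45, 80% power is reached at f = 0.1295.

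**The case against.** The strongest reply is that the trial will not run a Greenhouse–Geisser-corrected ANOVA. The primary model has only a random intercept, so it assumes compound symmetry and uses no ε, and the plan says openly that the ANOVA framework served for planning. On that view the relevant power at 45 is about 79%, close to target.

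Part of this stands: the 72% belongs to a test corrected for ε, and the restated text should say so. It does not rescue the figure:
- The paragraph names ε = 0.82 as an input and presents 44 as its result.
- If compound symmetry holds, the minimum is 46 and power at 45 is 79.1%. Both still miss the stated values, though narrowly.
- If ε really is 0.82, the uncorrected test in simulation rejected about 79% of the time at the planning effect, but about 6% of the time under the null. It reaches that power only by exceeding the stated α of 0.05.

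Two further points are fair. The shift in detectable effect, from 0.12 to about 0.13, is small beside the uncertainty in an effect size informed by a pilot with five participants per group. And the explanation of where 44 came from is an inference, because the software settings beyond the listed inputs are not given. Neither makes 44 correct.

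**Conclusion.** The concern holds. From the plan's own inputs the minimum for 80% power is 53 (54 balanced), 9 more than stated. The planned 45 give about 72% power for a valid 5% test at ε = 0.82, and 79% if the data are perfectly spherical. The result assumes the standard within–between interaction parameterisation, the stated inputs, and complete data on all 45 participants. The paragraph states no allowance for losses, and any loss would lower power further. The word approximately does not cover a gap of this size. The error affects the justification of the sample size and the reading of a null result; it does not affect the validity of the estimates.

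**What to change.** Rewrite the end of the sample-size paragraph:
- State that 45 participants (15 per group) give about 72% power for f = 0.12 at ε = 0.82 with a test corrected for non-sphericity, about 79% if ε = 1, and 80% power for f of about 0.13.
- Delete 44, or replace it with 53 (54 with equal groups).
- Say that these figures refer to the repeated-measures ANOVA used for planning, since the random-intercept model itself applies no ε.

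Enrolment need not change if the sponsor accepts the lower power. Keeping the 80% claim at f = 0.12 and ε = 0.82 would take 18 per group, 9 more participants than planned. The article says recruitment had not begun at submission, so the correction can be made before any data exist. The cost is protocol wording and a less favourable power statement.

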### Primary outcome

#### Maximal voluntary isometric contraction

Isometric peak force, expressed in kilogram-force (kgf), will be obtained during the MVIC maneuver. The MVIC of the elbow flexor muscles will be preceded by unilateral warm-up with submaximal isometric contractions (three repetitions lasting six seconds each) in all evaluation days. After warming up, each volunteer will be instructed to sit on a custom-made barbell curl bench with the shoulder joint angle at 45° of flexion and 0° of abduction. After positioning, the volunteers will pull a handle attached to a load cell (EMG System, São José dos Campos, São Paulo, Brazil). The elbow joint angle will be fixed at 90°, and the participant will be asked to flex the elbow joint as much as possible, keeping the forearm supinated. Participants will be instructed to flex the elbow as quickly and forcefully as possible upon hearing the verbal command “go”, sustain the contraction for five seconds, and then relax upon the command “stop”. A strong verbal command will be offered by the researchers [35]. This measurement will be performed three times before the pre-conditioning interventions, with a 45-s interval between attempts. The highest MVIC obtained during the baseline assessment will be considered the reference value. MVIC will be recorded in its original measurement scale for the primary analysis. For exploratory interpretation, post-exercise MVIC values will also be expressed as percentage change from baseline.

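### The primary MVIC model leaves each group's baseline mean free and measures the key effect as raw change, which is valid but gives up precision that a common-baseline model would recover

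*Protocol article*

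**What the plan says.** The Statistical analysis plan section of the Protocol article makes the group × time interaction the primary test. The model is "a linear mixed-effects model including group and time (treated as categorical factors) as fixed effects". Repeated values from one person are linked through a single random term per participant, the intercept. The contrast is also fixed: "The prespecified key contrast will be the between-group difference in change in MVIC from baseline to 72 h between the PBM and IPC groups". The same section then gives this difference in change as the effect measure for that comparison.

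The Maximal voluntary isometric contraction section adds that "MVIC will be recorded in its original measurement scale for the primary analysis". The sample-size paragraph counts five measurements, so baseline is a response and not a covariate. The article states neither a baseline covariate nor a common baseline mean.

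Under Study design and Ischemic preconditioning, the visit-2 MVIC test comes before any preconditioning. Allocation is randomised 1:1:1 with 15 participants per group.

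**The concern.** Because baseline MVIC is measured before the intervention in a randomised trial, the three groups have the same expected baseline. The planned model nevertheless estimates three baseline means and subtracts each group's own from its later values. Each subtraction adds baseline noise to the estimate. A model that uses the known equality, or adjusts for baseline, removes part of that noise.

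What is at stake is precision, not validity. The data needed are already collected. With 15 participants per group and a sample size rounded up only from 44 to 45, precision available at almost no cost is worth having. Recruitment had not begun when the article was submitted, so the change could still be prespecified.

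**Working it through.** **Inputs.** Within-participant correlation ρ = 0.79, f = 0.12, ε = 0.82, three groups, five measurements and N = 45, all from the Statistical analysis plan section. The baseline-to-72 h correlation is not given: "The pilot MVIC data yielded a within-participant correlation of 0.79", but the article itself notes "the absence of an IPC group and 72-hour assessment". Using 0.79 for that pair is an assumption. The formulas below take equal variances and compound symmetry, which is what a random intercept implies. The pilot's ε of 0.82 shows that this is only approximate.

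**The plan's own figure.** The noncentrality is λ = f²·N·m/(1−ρ), with df1 = (k−1)(m−1)ε and df2 = (N−k)(m−1)ε. At N = 45, λ = 0.0144 × 45 × 5 / 0.21 = 15.43. With ε applied to the degrees of freedom only, the minimum N is 44, as stated, and power is 81.0% at 44 and 82.1% at 45. This is the interaction with free baseline means, so the trial was sized for the analysis it plans.

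**Key contrast at 72 h.**
- Raw change: variance factor 2(1−ρ) = 0.420. SE of the group difference = √(2 × 0.420/15) = 0.237σ.
- Baseline-adjusted: variance factor 1−ρ² = 0.376. SE = √(2 × 0.376/15) = 0.224σ.
- Ratio of variances: (1+ρ)/2 = 0.895, a reduction of 10.5%. Since 45/0.895 ≈ 50, this is worth about 5 participants.
- In 20,000 simulated trials with 15 per group and a separately estimated baseline slope, the ratio was 0.917, a reduction of about 8%. Since 45/0.917 ≈ 49, this is worth about 4 participants.

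| Assumed baseline-to-72 h correlation | 0.5 | 0.6 | 0.7 | 0.79 | 0.85 | 0.9 |
|---|---|---|---|---|---|---|
| Variance reduction, 1 − (1+ρ)/2 | 25% | 20% | 15% | 10.5% | 7.5% | 5% |

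**Primary test.** Let d_t be the effect at each of the four post-exercise times and S their sum. The signal, up to a common factor, is Σd² − S²/5 with free baselines and Σd² − S²·ρ/(1+4ρ) with a common baseline. At ρ = 0.79, ρ/(1+4ρ) = 0.79/4.16 = 0.190.

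| Shape of effect | Free baseline | Common baseline | Gain |
|---|---|---|---|
| Constant at all four times | 4 − 16/5 = 0.800 | 0.962 | 20.2% |
| Growing linearly | 0.625 | 0.688 | 10.1% |
| Equal at 24, 48 and 72 h only | 1.200 | 1.291 | 7.6% |
| 48 and 72 h only | 1.200 | 1.240 | 3.4% |
| 72 h only | 0.800 | 0.810 | 1.3% |

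With ε on the degrees of freedom only, power at N = 45 goes from 82.1% to between 82.7% and 89.5%, depending on the shape.

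**Baseline imbalance.** If two groups differ by Δ at baseline by chance, the change contrast is off by −(1−ρ)Δ = −0.21Δ. The standard deviation of Δ is √(2/15) = 0.365σ. A one-SD imbalance therefore moves the contrast by about 0.08σ, a third of its SE of 0.237σ.

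**The case against.** The strongest reply is that nothing here is an error. The planned model is unbiased under randomisation, and the sample size was calculated for the same free-baseline interaction, so there is no shortfall against plan. The saving in standard error is about 5%. It rests on a correlation from a pilot with five participants per group and no 72 h visit. All of that stands, and it is why the point is limited to efficiency.

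It can also be said that the stated effect measure is not itself at fault. Under a common baseline mean, the difference in change equals the adjusted difference at 72 h. That is correct: the loss comes from leaving the baseline means free. A separate analysis plan might add the constraint, but the article already names the model, the test and the contrast, and read plainly they do not include it.

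A reader might infer three stronger claims that the documents do not support:
- **That a fifth of the primary test's signal is wasted.** The 20% is a gain; as a loss it is 1 − 0.800/0.962 = 16.8%. It applies only to an effect constant over all four times, and the article fixes no such shape.
- **That baseline imbalance passes straight into the change.** Only about a fifth of it does, with opposite sign.
- **That power is already below 80%.** This depends on how ε enters. Power at N = 45 is 82.1% with ε on the degrees of freedom only, 79.1% with ε = 1, and 72.5% with ε on the noncentrality as well. That is a separate matter.

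**Conclusion.** The point holds as a worthwhile and nearly free gain in efficiency. The planned analysis is valid, but it treats as unknown something that randomisation guarantees. The expected reduction in the variance of the key contrast is about 8 to 10%, assuming a baseline-to-72 h correlation of 0.79, equal variances and compound symmetry. Under equal variances it is positive for any correlation below 1 before allowing for the cost of estimating a slope, and it shrinks as the correlation rises. For the primary test the gain in noncentrality at ρ = 0.79 lies between about 1% and 20%, and where it falls depends on an effect profile that the article does not specify. None of this implies bias, a failed sample-size calculation or an invalid primary test.

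**What to change.** Prespecify a constrained longitudinal model: one common baseline MVIC mean for all groups, with group-by-time terms at the four post-exercise times only. Make the primary test the joint test that the groups are equal at all four times, with (3−1) × 4 = 8 df.

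Equivalently, use the four post-exercise values as responses with baseline MVIC as a covariate, and test group and group × time together (2 + 6 = 8 df). The post-exercise interaction must not be tested alone: for a benefit that is constant over those times its signal is zero.

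Report the key contrast as the baseline-adjusted PBM−IPC difference at 72 h, with its 95% confidence interval.

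The cost is small. No new data are needed, and the mixed-model likelihood approach to missing values is kept. The primary test has to be reworded, and the sample-size paragraph should say that its calculation was made for the unadjusted group × time interaction. The change should be fixed before any outcome data are seen.

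### The primary model's random intercept assumes sphericity (ε = 1), whereas the sample size was planned with ε = 0.82, so non-sphericity is allowed for in planning but not in analysis.

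*Protocol article*

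**What the plan says.** All the relevant text is in the protocol article, section Statistical analysis plan.

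- **Primary test.** "The primary inferential test will be the group × time interaction from a linear mixed-effects model", with group and categorical time as fixed effects, "with a participant-specific random intercept to account for within-participant correlations". The key contrast is the PBM versus IPC difference in MVIC change from baseline to 72 h, reported with a 95% confidence interval.
- **Pilot.** "The pilot included 20 participants (five per group) allocated to placebo, 6 J, 24 J, or 72 J PBM". Force was measured at four times, the last at 48 h. On ε and the other planning values, the pilot "yielded a within-participant correlation of 0.79, a Greenhouse–Geisser correction of ε = 0.82, and an observed group × time effect of f ≈ 0.23".
- **Sample size.** Three groups with "five measurements, α = 0.05, 80% power, f = 0.12, a within-participant correlation of 0.79, and ε = 0.82", giving about 44 participants, so 45 are planned (15 per group).
- **Checks.** Residual plots, Shapiro–Wilk, influence and model fit are to be examined. The text does not say what follows if the covariance structure fits poorly.

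**The concern.** When time is categorical and a random intercept is the only device for within-person dependence, every time point has the same variance and every pair of times the same correlation. That is compound symmetry, which implies ε = 1. The planning paragraph uses ε = 0.82 for the same test. The plan justifies the mixed model partly by its handling of within-participant correlation, yet with complete balanced data this model gives the uncorrected repeated-measures F test. The adjustment made at the design stage is lost at analysis.

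Two results depend on the assumption: the size of the primary interaction test, and the coverage of the headline interval. The interval's standard error comes from a residual variance averaged over all time pairs, not from the variability of the baseline-to-72 h change itself.

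**Working it through.** **Inputs from the protocol.** k = 3 groups, m = 5 times, N = 45 (15 per group), α = 0.05, f = 0.12, mean correlation ρ = 0.79, ε = 0.82. Pilot: 20 participants in 4 groups (20 − 4 = 16 error df), 4 times.

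**1. The plan's own figure.** For the interaction, λ = f²·N·m·ε/(1−ρ), df1 = (k−1)(m−1)ε and df2 = (N−k)(m−1)ε. At N = 44, λ = 0.0144 × 44 × 5 × 0.82/0.21 = 12.37, df = 6.56 and 134.5, and power is 71.2%. This version needs N = 53. With ε applied to the degrees of freedom only, λ = 15.09, power at 44 is 81.0%, and the minimum is 44. The stated 44 is therefore matched only under the second convention. The software settings should be checked before that figure is called wrong, and the present point does not depend on it. What matters here is that ε = 0.82 was a planning input.

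**2. Size of the interaction test if ε = 0.82.** The random-intercept test uses df = 8 and 168, with critical F = 1.99. Box's approximation refers the statistic to F with 8ε and 168ε df, that is 6.56 and 137.8, where the 5% critical value is 2.11. The chance of exceeding 1.99 is then 6.4%. Simulations of 40,000 null trials per structure gave 6.1–6.6% (simulation standard error about 0.12 points), so roughly 6.2–6.5%. For comparison, Box gives 5.8% at ε = 0.9 and 7.7% at ε = 0.7.

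**3. Size of the baseline-to-72 h contrast.** The model takes the variance of any change as 2(1 − 0.79)σ² = 0.42σ², with 168 df (critical t = 1.974). The structures below are assumptions. In the first two rows one time correlates 0.705 with the other four, and those four correlate 0.847 with each other. The mean correlation is (4 × 0.705 + 6 × 0.847)/10 = 0.79, and ε = 0.82.

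| Assumed structure | True variance of change | True SE / model SE | Type I error |
|---|---|---|---|
| Baseline is the odd time | 2(1 − 0.705)σ² = 0.59σ² | √(0.59/0.42) = 1.19 | 9.8% (simulated 9.9%) |
| Immediate-post is the odd time | 2(1 − 0.847)σ² = 0.306σ² | √(0.306/0.42) = 0.85 | 2.2% (simulated 2.2%) |
| Correlation decays with time | – | 1.16–1.21 | 9.3–10.8% |

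When the standard error comes from the changes themselves (42 df), as an unstructured covariance in effect provides, simulated size is 5.0–5.2% in every structure tried.

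**4. What the pilot can show about ε.** Simulated pilots with exact sphericity, 16 error df and 4 times give Greenhouse–Geisser estimates averaging 0.84 (5th–95th percentile 0.70–0.95), and 36–37% of them are 0.82 or lower. The Huynh–Feldt-type value, with p = 3, is [(17 × 3 × 0.82) − 2]/[3 × (16 − 3 × 0.82)] = 39.82/40.62 = 0.98. At ε = 0.98 the interaction test has size 5.1%.

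**The case against.** The strongest reply is that 0.82 is about what a pilot of this size returns when sphericity is true (step 4). Its use in the sample size can then be read as caution, not as evidence of a departure. This stands. A reader might infer that the sponsor's own data contradict the random-intercept model, and the documents do not support that.

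The reply also holds on three further points. The inflation of the interaction test at ε = 0.82 is modest, about 1.4 percentage points. ε does not determine the error of the 72 h interval, so a flat statement that coverage is below 95% would go too far. And the plan mentions maximum likelihood ("using maximum likelihood estimation under a missing-at-random assumption") but names no reference distribution, so figures for a Wald chi-square test would rest on a choice it does not state.

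It could also be said that naming a random intercept does not exclude a structured residual covariance, and that model fit will be examined. This carries less weight. The random intercept is the only device the plan gives for within-participant correlation, and no alternative or consequence is attached to the checks. The listed residual plots and normality test do not assess the correlation pattern. This is a choice made in the text, not a detail merely left for elsewhere.

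The point does not extend to the secondary outcomes. They are exploratory, no random-intercept structure is fixed for them, and generalized mixed models are foreseen for ordinal or bounded scales when Gaussian assumptions fail.

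**Conclusion.** The point holds as an inconsistency with conditional consequences. The analysis assumes ε = 1, while planning used 0.82. If 0.82 is the true value, the primary test runs at about 6.2–6.5% instead of 5%. At that same ε, the error rate of the key 72 h contrast ranged from about 2% to about 10–11% across the assumed structures, so the interval may be too wide or too narrow. The pilot had no 72 h assessment and cannot settle which.

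These figures assume complete data, 15 participants per group and a random intercept with independent residuals. The contrast figures also rest on the structures stated. Severity is moderate: non-sphericity is not demonstrated, but the plan gives no basis for relying on its absence in its headline interval.

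**What to change.** For the primary MVIC analysis, replace the random intercept with an unstructured within-participant covariance over the five times, fitted by REML with Kenward-Roger degrees of freedom. It has 5 × 6/2 = 15 parameters, to be estimated from 45 participants. Name the fallback order in advance in case it does not converge, for example heterogeneous Toeplitz, then a random intercept with a small-sample robust variance.

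This takes about a sentence in the analysis section. It leaves fewer error degrees of freedom. For the contrast, going from 168 to 42 df moves the critical t from 1.974 to 2.018, about 2% on the interval's half-width. The fallback may also be needed, particularly with missing visits. The Study design section says recruitment had not begun at submission; if that is still so, the structure can be fixed before any trial data exist.
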